## Abstract

**Introduction:** Once-weekly or once-monthly injectable depot buprenorphine is a new opioid substitution treatment (OST) medication that provides clinically relevant plasma concentrations without daily peaks. Together with a high tolerability and acceptance reported by patients, the prolonged release of injectable depot buprenorphine might have beneficial implications on the patients' quality of life and social participation. The primary objective of this prospective non-interventional observational study is to evaluate the effects of subcutaneous injectable depot buprenorphine on the quality of life of patients in routine OST care in Germany. Secondary outcomes like illicit substance use, psychological distress, social participation and activity are assessed to provide an overall evaluation toward addiction recovery.

**Methods and Analysis:** The present study is a non-randomized prospective observational study with a control group (treatment-as-usual). To ensure comparability between both patient groups, suitable control patients (*n* = 213) from the same OST unit will be matched pairwise to each patient treated with injectable depot buprenorphine (*n* = 213). Matching variables are gender, duration of OST, take-home prescription and psychosocial functioning (according to the Global Assessment of Functioning scale). Primary study endpoint is the difference of change in quality of life, assessed with the recently developed Opioid Substitution Treatment Quality of Life scale (OSTQOL), within the depot buprenorphine group between baseline and month 12. The primary analysis will be carried out according to the intention-to-treat principle (ITT) by comparing OSTQOL mean scores using dependent *t*-tests. For secondary analyses, group comparisons will be done by mixed model approaches with baseline OSTQOL score and the (pairwise) cluster term as covariates.

**Discussion:** The study combines clinical, routine OST care data with relevant patient reported outcome data. The pairwise matching allows conclusions on effects of different OST medications. The study findings will provide new insights in the addiction recovery processes of OST patients treated with depot buprenorphine.

**Ethics and Dissemination:** The study protocol has been approved by the Ethics Committee of the Hamburg Chamber of Physicians (Ärztekammer Hamburg) (reference number: PV7078). The study results will be disseminated through peer-reviewed publications and presentations on scientific conferences.

**Clinical Trial Registration:** German Clinical Trials Register DRKS-ID: DRKS00020797

## Introduction

Opioid dependence is a chronic relapsing disease that is associated with a high health burden and enormous social consequences for the patient (1). In terms of accessibility, retention and effectiveness, opioid substitution treatment (OST) has become the primary option for the treatment of opioid dependence in Germany. As of July 1st, 2019, 79,700 opioid-dependent persons in Germany were registered in OST (2). While OST decreases drug-related deaths and reduces illicit opioid use, the effectiveness of OST remains limited with regard to the other objectives of the respective German Medical Association guidelines (3), e.g., abstinence from opioids, the stabilization of health, and an improvement in social participation (1, 4). The rate of OST patients in Germany who regularly terminate OST with opioid abstinence is low (1, 4–6) and the health and social burden remains high among many patients even after years in OST (1, 4, 7). Given the wide-ranging health and social impact of opioid dependence and the limitation of traditional health parameters to reflect the complexity and severity of the condition, patient-related outcome measures (PROMs) such as quality of life are needed to measure the holistic and integrative approach of OST (8–10) and to inform about the course of treatment and addiction recovery processes within OST (11).

Clinical trials have shown that the sustained release of the newly approved once-weekly or once-monthly injectable subcutaneous depot buprenorphine formulations produce an immediate and sustained opioid blockade and efficiently suppress opioid withdrawal after the first injection (12, 13). After the subcutaneous injection the depot buprenorphine transforms into a liquid-crystalline gel matrix that encapsulates buprenorphine and releases it in controlled and steady rates. The gel-like depot is biologically degraded over time, which minimizes the initial burst-like release of oral buprenorphine (14–16). Depot buprenorphine with different doses and dosing frequencies enables more flexible and individualized therapies of opioid use disorders across all treatment stages, from initiation and stabilization to long-term maintenance and preparation for regular OST termination.

A pharmacokinetic evaluation shows clinically relevant plasma concentrations of buprenorphine without daily peaks, which suggests potential benefits of injectable depot buprenorphine in the avoidance of withdrawal symptoms (17). Accordingly, patients reported higher acceptability of injectable depot buprenorphine compared with the sublingual formulation (17). The long-acting formulation together with pharmacokinetic profiles and the high tolerability and acceptance reported by patients indicate that injectable depot buprenorphine can have beneficial implications on the patients' adherence as well as quality of life (17).

Previous literature compared changes in quality of life between depot buprenorphine and placebo (18, 19). Compared with placebo, patients receiving extended-release injectable buprenorphine showed significantly improved patient-reported outcomes with regard to health and medication satisfaction after 6 months (18). Moreover, their employment rate after 6 months increased, whereas the number of hospital days per person-year decreased (18). The 12-month follow-up confirmed that OST with subcutaneous injected buprenorphine can result in high retention and abstinence rates as well as in improved social aspects like employment (19).

In contrast to previous literature, this study will take a more naturalistic approach, by comparing not only against placebo, but against treatment as usual (TAU), which includes all registered OST medications, such as methadone or levomethadone, sublingual buprenorphine or slow-release oral morphine. By comparing against other forms of OST, including sublingual buprenorphine, we aim to evaluate the potential advantages that are specifically related to the depot formulation, e.g., the decrease of doctor-patient contacts, which might support patients' independence and social participation. In addition to generic quality of life and mental health instruments, we will use the new Opioid Substitution Treatment Quality of Life scale (OSTQOL) (20) as our main outcome measure, to account for the whole range of aspects of recovery that are relevant for opioid-dependent patients (20).

## Methods and Analysis

### Objectives

The primary objective of this study is to evaluate the quality of life among patients substituted with subcutaneous injectable depot buprenorphine. Secondary objectives include treatment satisfaction, acceptance of injectable depot buprenorphine and its application form, illicit substance use, retention in treatment, craving, psychological distress, social participation and activity, and cost-effectiveness. The primary and secondary objectives are selected to provide an overall assessment toward addiction recovery.

### Hypothesis

OST with once-weekly or once-monthly injectable depot buprenorphine will result in increased quality of life, as measured by the Opioid Substitution Treatment Quality of Life scale (OSTQOL) (20) between baseline (t_0_) and month 12 (t_4_).

### Study Design

The study objectives will be evaluated in a non-randomized prospective non-interventional observational study with control group design (treatment-as-usual, TAU). All OST patients with TAU (i.e., treated with any registered OST medication, but not with injectable depot buprenorphine (e.g., racemic methadone, levomethadone, sublingual buprenorphine or slow release oral morphine) can take part in the control group. In order to avoid a selection bias and to ensure an overall comparability of the patient groups (injectable depot buprenorphine vs. TAU), one suitable patient from the OST unit will be pairwise matched to each recruited depot buprenorphine patient. Matching variables are gender (male /female), duration of OST (years), take-home prescription (yes /no) and patients' functioning measured by the global assessment of functioning scale (according to percentiles measured by the Global Assessment of Functioning Scale, GAF). Prior to matching, all patients from each participating OST unit will be screened for these four criteria based on an anonymized list of patients. After inclusion of a depot buprenorphine patient, a respective OST patient who is not willing to switch to depot treatment will be asked to participate as control group patient. An overview of the study design is provided in Figure 1.

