### Patient Recruitment

The study will be carried out in OST units (specialized primary care practices or addiction outpatient clinics) with OST physicians experienced in the substitution treatment of opioid-dependent patients. All patients who start OST with injectable depot buprenorphine or who have the intention to switch from a previous OST medication to injectable depot buprenorphine will be informed by the OST physician about the possibility to participate in the study. The decision to be treated with injectable depot buprenorphine has to be made in advance and independently of study participation. All patients who fulfill the inclusion criteria will receive the detailed study information. The matching and recruiting process will be documented by lists, including the assignment of the patient and the code number. The recruitment lists will be kept in the OST unit and will be treated confidential. Only staff from the OST unit will have access to the recruitment lists. The inclusion of a patient will be documented on a specific form and will be faxed or sent as a scan to the study center (ZIS).

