## Discussion

The primary objective of this non-randomized prospective observational study is to evaluate the effects of subcutaneous injectable depot buprenorphine on the quality of life of opioid dependent patients in routine OST care in Germany. Together with the secondary objectives, the study aims to provide an overall assessment toward addiction recovery among OST patients treated with subcutaneous injectable depot buprenorphine. The main strength of the study and added value to previous research is this holistic approach in the study objectives and respective variables. By combining clinical OST routine care data with patient-reported outcomes, and comparing depot buprenorphine against other OST medications, this study will help to estimate the impact of depot buprenorphine on quality of life and recovery under real-world conditions.

At the same time, this naturalistic design bears some limitations, most importantly the lack of randomization. OST patients with the decision to switch to subcutaneous injectable depot buprenorphine might differ from other OST patients in several aspects, such as disease severity and psychosocial functioning. To minimize potential selection biases, a matched pair control group design was selected to ensure that OST patients in the depot buprenorphine group will not significantly differ from those in the control group with respect to gender, duration of OST, take-home prescription and psychosocial functioning (GAF-percentiles). A second advantage of the matched-pair design is that OST units in Germany are organized in different primary care settings and vary in the provision of health and psycho-social care as well as in the number of patients per unit. As the number of OST patients in the depot buprenorphine group per unit might be low, a pairwise matching of control patients from the same OST unit was selected instead of a cluster-randomized controlled trial design with a fixed number of patients per cluster.

Another limitation consists in the heterogeneity of the TAU group, especially in terms of OST medication. A comparison between depot buprenorphine and sublingual buprenorphine only would help to identify effects of the application form. However, as (levo-)methadone is still the most frequently used OST agent in Germany (BfArM 2020) (2), we preferred not to exclude this large patient group and adhere to our naturalistic and observational approach.

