#### Patient Information and Informed Consent

To be eligible for study participation, all patients have to provide their written consent after having been informed in detail about the study objectives, nature, extent and risks. The date of the written consent has to be noted. Prior to consent, no investigations, surveys or other measures associated with the study will be conducted.

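### Pre-consent screening for the match conflicts with the consent rule as worded, and the group-comparison model does not adjust for the matching variables

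*Protocol article*

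**What the plan says.** The Study Design section of the protocol article matches each depot patient to one control from the same OST unit. The four criteria are gender, years in OST, take-home prescription and "patients' functioning measured by the global assessment of functioning scale", the last by percentiles. On the order of events it states: "Prior to matching, all patients from each participating OST unit will be screened for these four criteria based on an anonymized list of patients". After a depot patient has been included, "a respective OST patient who is not willing to switch to depot treatment will be asked to participate as control group patient".

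The section on patient information and informed consent states: "Prior to consent, no investigations, surveys or other measures associated with the study will be conducted".

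The Patient Recruitment section says: "The matching and recruiting process will be documented by lists, including the assignment of the patient and the code number". The lists stay in the unit: "Only staff from the OST unit will have access to the recruitment lists". For the study centre, "The inclusion of a patient will be documented on a specific form and will be faxed or sent as a scan".

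The Variables section names gender among the sociodemographic items and gives medication and doses as the OST data. GAF, OST duration and take-home status appear neither there nor in Table 2. Under Secondary Outcome Analyses, the depot-versus-control comparison is a mixed model with two adjustment terms, baseline OSTQOL and the pair. The Discussion says that, through matching, depot patients "will not significantly differ from those in the control group with respect to gender, duration of OST, take-home prescription and psychosocial functioning (GAF-percentiles").

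**The concern.** There are two separate issues.

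The first is a conflict of wording. Reviewing a whole unit against study criteria is naturally read as a measure associated with the study. It happens before any control has been asked, and it covers patients who will never be asked. The consent section allows no exception. Sites and ethics committees reading both sections cannot tell what may be done before consent, in particular whether staff may rate GAF for the purpose of the match.

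The second is statistical. The design relies on matching as its main protection against selection bias in the group comparison. Matching on years in OST and on GAF percentiles is unlikely to be exact, and pairs lose members during follow-up. The stated model contains none of the matching variables, and three of the four are not named among the data collected at baseline. What matching leaves unbalanced therefore stays in the estimated difference between depot buprenorphine and treatment as usual.

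**Working it through.** **1. Order of events.** Screening of the unit comes first, then inclusion of a depot patient, then the approach to a control, then that control's consent. Screening thus precedes every control's consent. The consent section excludes study-associated measures at that stage. The two fit together only if screening means reading values already held in routine records by the treating staff. The article does not limit it in this way. It does not describe GAF as routine data, and the routine OST data that it names are medication and doses.

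**2. The term for the list.** A particular patient has to be invited, and the unit's lists hold the link between patient and code number. A list with such a key is pseudonymised. The section on handling adverse events uses that term for its own documentation.

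**3. The matching variables through the plan.**

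| Matching variable | Named in Variables or Table 2 | In the group-comparison model |
|---|---|---|
| Gender | yes | no |
| OST duration (years) | no | no |
| Take-home prescription | no | no |
| GAF (percentiles) | no | no |

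**4. What the pair term does and does not remove.** In a complete pair, the pair term removes whatever the two members share. A yes/no variable that is matched exactly, such as gender or take-home status, leaves no difference at enrolment. OST duration and GAF percentile can still differ within the pair. The part of the group difference due to such a variable is

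residual bias = (effect of the variable on the outcome, given baseline OSTQOL) × (mean within-pair difference in the variable).

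Adding the variable as a covariate removes this term to the extent that its effect is modelled correctly. Where one member is missing, the result depends on how the pair term is fitted, which the article does not state. As a fixed effect, the remaining member adds nothing to the group contrast at that visit. As a random effect, it does contribute, through a comparison between pairs that matching no longer balances. Then all four variables matter.

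**5. How many pairs could be broken.** First the plan's own figures:

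- Paired t-test, d = 0.25, two-sided α = 5%, power 80%: n = 127.5, so 128, as stated.
- 40% drop-out: 128 / 0.6 = 213.3; the plan states 213. Two arms: 2 × 213 = 426, as stated.
- Detectable group difference: d = 0.352 with 128 per arm and d = 0.272 with 213 per arm. The stated 0.35 therefore corresponds to 128 per arm, that is, to 40% loss in both arms.

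Now apply 60% retention in each arm to 213 pairs, counting observed month-12 data before any imputation. The documents do not say how drop-out is related within pairs, so a range is shown:

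| Assumption on drop-out within pairs | Both observed | Exactly one observed |
|---|---|---|
| Members always drop out together | 0.60 × 213 = 128 | 0 |
| Independent | 0.6 × 0.6 × 213 = 77 | 2 × 0.6 × 0.4 × 213 = 102 |
| Never together | 0.20 × 213 = 43 | 0.80 × 213 = 170 |

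Under independence, pairs with one observed member outnumber complete pairs at month 12. The mixed model also uses earlier visits, so these patients are not wholly lost, but at month 12 the balance rests on fewer intact pairs than the enrolment figure suggests.

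**The case against.** The strongest reply on consent is that nothing in the article says a patient is contacted or newly rated before consent. Treating staff who compile a list from their own records may see no breach. That is a fair reading, and it makes this a matter to reconcile rather than a proven violation. It still has to be written down, because GAF is a rated scale and the consent rule is absolute.

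On the data, an article may leave the content of the inclusion form and the CRF to the full protocol, and Table 2 lists outcome domains, so GAF need not appear there. This stands: the article does not show that the values go unrecorded. The model is different, because the article does state its adjustment terms and the matching variables are not among them. Baseline OSTQOL will absorb part of any imbalance, but not necessarily all of it.

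Three stronger readings are tempting and are not supported:

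- A reader might infer that an anonymised list leaves the unit unable to find the patient to invite. The lists described under Patient Recruitment link patient and code, so staff can.
- A reader might infer that balance cannot be verified. Gender is collected, baseline characteristics and OST data are to be described, an inclusion form goes to the study centre, its staff monitor on site, and the pair link must reach the analysis data. The access limit is stated for the recruitment lists, not expressly for the matching values.
- A reader might infer that matching values grow stale over the recruitment period. The article does not say that the list is drawn up once and frozen, so no age can be given to the values and no rate of mismatch derived.

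**Conclusion.** The point holds in a limited form. The Study Design and informed-consent sections conflict as worded and should be reconciled, and the list should be called pseudonymised. The group-comparison model leaves unadjusted any imbalance in the matching variables that remains within pairs or arises when pairs are broken. Three of the four variables are not named among the baseline data that such an adjustment would need.

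The size of any bias cannot be derived: the documents give neither the closeness of the match nor the effect of these variables on outcome. The counts of broken pairs rest on the plan's 40% drop-out holding in both arms and on the stated assumptions about dependence within pairs.

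Only the secondary depot-versus-control comparisons are affected. The primary endpoint is change within the depot group, and neither it nor its sample size depends on the match. This is a worthwhile, inexpensive improvement, not a fault that undermines the main analysis.

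**What to change.** - **Study Design and informed consent.** State that pre-selection before consent uses only values already in the unit's routine records, and that any GAF rating made for the study follows consent. Word the consent section to match. Replace *anonymized* by *pseudonymised*.
- **Variables.** Record gender, OST duration, take-home status, GAF and the pair code at t0 in the CRF for both members of each pair. Recruitment has already begun, so for pairs already enrolled, transfer the values used for matching under the code number.
- **Secondary Outcome Analyses.** Report balance on the four variables at baseline, and again among patients observed at month 12. Add the matching variables, at least OST duration and GAF, as covariates in the mixed model, and state whether the pair term is fixed or random. Settle this before group outcomes are examined.

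The cost is a few CRF items, wording changes in a handful of sections, an ethics notification and a few model parameters. Sample size, treatment and the primary analysis are unchanged.

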**Figure 1 F1:**
[figure not shown]
CONSORT diagram on enrollment, allocation, follow-up and analyses.

### Primary Outcome Measure

The **primary endpoint** of the study is the change in quality of life measured by the difference of OSTQOL total score between baseline (t_0_) and month 12 (t_4_) in the depot buprenorphine group.

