### Secondary Outcome Measures

Secondary endpoints include the difference in the OSTQOL score between depot and control group at month 12 (t_4_), comparisons between the depot and control group in patient satisfaction (Client Satisfaction Questionnaire–CSQ-8) at month 12 (t_4_), substance use (i.e., on the basis of self-reporting) at month 6 (t_3_) and month 12 (t_4_), the retention rate in treatment at month 12 (t_4_), psychological distress (Brief Symptom Inventory 18) at t_4_, social participation at month 6 (t_3_) and month 12 (t_4_) as well as the cost-effectiveness (on the basis of quality-adjusted life years (QALYs); EuroQOL five dimensions questionnaire (EQ-5D) at month 12 (t_4_). Three secondary endpoints will be measured solely in the depot group, the acceptance of the depot medication and its application measured by the Treatment Satisfaction Questionnaire for Medication (TSQM-14) at month 1, 3, 6 and 12 (t_1_-t_4_), the dosage adequacy measured by the Opiate Dosage Adequacy Scale (ODAS) at month 1, 3, 6 and 12 (t_1_-t_4_) and changes in quality of life domains (OSTQOL subscales) in depot group over time between baseline (t_0_) and month 12 (t_4_). Possible adverse reactions will be assessed by a physician and recorded as part of the documentation of adverse events (AEs) and adverse drug reactions (ADRs). An overview of all primary and secondary outcome measures is provided in Table 1.

**Table 1 T1:** Overview of primary and secondary outcome measures.

**Primary outcome measure**	**Difference of OSTQOL total score in depot group between baseline (t_0_) and month 12 (t_4_)**
**Secondary outcome measures**	1. Quality of life (OSTQOL score) between depot and control group at t_4_ 2. Acceptance (TSQM-14) of injectable depot buprenorphine between t_1_ and t_4_ 3. Patient satisfaction with OST care (CSQ-8) between depot and control group at t_1_- t_4_ 4. Dosage adequacy (ODAS) in depot group at t_1_-t_4_ 5. Substance use (i.e., self-reporting) between depot and control group at t_3_ and t_4_ 6. Psychological distress (BSI-18) between depot and control group at t_4_ 7. Social participation between depot and control group at t_4_ 8. Retention rate (percentage of patients) in depot group at t_3_ and t_4_ 9. Cost-effectiveness [on the basis of quality-adjusted life years (QALYs); EQ-5D] between depot and control group at t_4_ 10. Changes in quality of life domains (OSTQOL subscales) in depot group between baseline (t_0_) and month 12 (t_4_)

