### Treatment

The depot arm of the study will include opioid-dependent patients who are willing to switch or to initiate OST with one of two injectable depot buprenorphine formulations (once weekly or once monthly). Thus, this includes newly admitted patients who are starting with OST, as well as patients who are already in treatment (e.g., with racemic methadone, levomethadone, sublingual buprenorphine, slow release oral morphine). The participation in the study is voluntary and non-participation will not incur disadvantages neither for the physician (or the OST unit) nor for the patient. In this respect, there will be no increased risk resulting from study participation. Patients who were facing problems with their previous OST medication might benefit from study participation, and probably show an increased acceptance and willingness to use subcutaneous, injectable depot buprenorphine. Further, OST providers might benefit from expanded, more individualized therapeutic options for OST patients. Based on the clinical experiences gained so far, injectable depot buprenorphine is highly accepted by patients, and its side effect profile is comparable to sublingual buprenorphine with few, mild and reversible injection site reactions (17).

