#### Primary Outcome Analysis

The main analysis will be carried out according to the intention-to-treat principle (ITT), considering all patients who have started the substitution treatment with injectable depot buprenorphine. The primary outcome measure is the difference of OSTQOL (20) scores between baseline (t_0_) and month 12 (t_4_) in the depot group. The average OSTQOL mean score will be compared between these time points and analyzed for statistical significance using dependent *t*-tests. It is tested against the statistical null hypothesis (H0) of a decrease or no change in the OSTQOL mean score. The alternative hypothesis (H1) consists in a significant improvement of the OSTQOL mean score, which corresponds to an improvement in quality of life of the patients.

H0: M (Month 12) ≤ M (baseline) (OSTQOL mean score at 12 months ≤ baseline OSTQOL mean score)H1: M (Month 12) > M (baseline) (OSTQOL mean score at 12 months > baseline OSTQOL mean score).

The hypothesis will be tested two-sided at a significance level of *p* < 5%. The statistical analyses will be made according to the intention-to-treat (ITT) as well as to the per-protocol (PP) principle. The PP sample is defined by all patients who have undergone OST with injectable subcutaneous depot buprenorphine for at least 12 months and for whom sufficient baseline and 12-month data are available. The ITT sample comprises all patients who provided a written consent, who have undergone the baseline assessment, and–for patients in the depot study arm–who have received the first dose of injectable depot buprenorphine. For the ITT analysis, data from all study patients will be used independently of their status in or out of treatment with injectable depot buprenorphine. Missing values at the 12-month time point will be replaced by missing imputation procedures. These may either include last observation carried forward (LOCF) approaches or longitudinal mixed model analyses using all available follow-up assessments. The choice of imputation procedures for the ITT analysis will depend on the proportion of missing values at the 12-month time point as well as the quantity of available data at 3-month and 6-month follow-up, and will be determined by sensitivity analyses.

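### The primary test is an uncontrolled before-after change in the depot arm but is presented as an effect of depot buprenorphine; an effect claim should also require the planned comparison with matched controls

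*Protocol article*

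**What the plan says.** The section Primary Outcome Measure sets the primary endpoint as change in quality of life "measured by the difference of OSTQOL total score between baseline (t_0_) and month 12 (t_4_) in the depot buprenorphine group". Under Primary Outcome Analysis, the baseline and month-12 means are to be "analyzed for statistical significance using dependent *t*-tests". The hypothesis has no control term: "It is tested against the statistical null hypothesis (H0) of a decrease or no change in the OSTQOL mean score".

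The wording of the aim varies. The Objectives section is neutral and speaks of evaluating quality of life in patients on depot buprenorphine. The Discussion is causal: "The primary objective of this non-randomized prospective observational study is to evaluate the effects of subcutaneous injectable depot buprenorphine on the quality of life". The Abstract uses the same causal form, and the Hypothesis section predicts that depot treatment will bring about higher quality of life.

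The study follows 213 pairwise-matched controls from the same treatment units. Among the secondary endpoints is "the difference in the OSTQOL score between depot and control group at month 12 (t_4". Secondary Outcome Analyses specifies a mixed model for it, with baseline OSTQOL and the pair as covariates. The Sample Size Calculation gives d = 0.25, 128 evaluable and 213 recruited depot patients for the primary test, and d = 0.35 as the detectable difference between groups.

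The Treatment section says of the depot arm that "this includes newly admitted patients who are starting with OST", alongside patients who switch from another medication. The limitations in the Discussion cover lack of randomisation, the mixed control medications and the 12-month horizon. They do not mention that the primary test has no comparator.

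**The concern.** A paired test asks whether depot patients score higher at month 12 than at baseline. It does not ask whether they score higher than they would have on another medication. Several things can raise the month-12 mean without any depot-specific benefit: starting substitution treatment at all (for newly admitted patients), time trend, attention from follow-up, and regression to the mean if some patients switch at a low point.

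The headline conclusion is at stake. With the causal wording in the Abstract, Hypothesis and Discussion, a significant primary result would naturally be reported as an effect of depot buprenorphine, which the test does not identify. The comparison that bears on that question is already planned and sized, but nothing makes an effect claim depend on it.

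**Working it through.** **Inputs from the Sample Size Calculation.** Alpha 5%, power 80%, d = 0.25, 128 evaluable, 40% drop-out, 213 recruited per arm, between-group d = 0.35. The primary test is two-sided according to Primary Outcome Analysis.

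**Step 1: reproduce the plan's figures.**
- Paired t-test, two-sided 5%, d = 0.25: the noncentral t-distribution gives n = 128 with power 80.2%. The normal approximation ((1.960 + 0.842)/0.25)² = 125.6 gives 126. One-sided versions give 99 to 101 and do not match.
- Drop-out: 128/(1 − 0.40) = 213.3, stated as 213.
- Between groups, 128 per arm: (1.960 + 0.842) × √(2/128) = 0.350, as stated.

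All three reproduce. The 128 is a one-sample size for the before-after change, with no control arm in it.

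**Step 2: how often the primary test succeeds with no depot advantage.** Suppose both arms improve by the same standardised change δ, in units of the SD of change. The true depot-minus-control difference is then zero. The paired t statistic has noncentrality δ√128 = 11.31δ on 127 degrees of freedom. The documents do not give δ for this population, so a range is shown.

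| Shared change δ | Noncentrality | Significant improvement on the primary test |
|---|---|---|
| 0 | 0 | 2.5% |
| 0.10 | 1.13 | 20% |
| 0.15 | 1.70 | 39% |
| 0.20 | 2.26 | 61% |
| 0.25 | 2.83 | 80% |
| 0.40 | 4.53 | 99% |

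In simulations with δ = 0.10, 0.25 and 0.40, a two-sample test between the arms kept its two-sided error at 5.0% to 5.2%.

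**Step 3: is the range plausible on the protocol's own evidence?** The Sample Size Calculation cites a 12-month quality-of-life gain of d = 0.40 in patients who switched to buprenorphine/naloxone, and d = 0.80 at 12 months under diamorphine. Neither is a depot product, and both exceed the planned 0.25. These are other instruments and populations, and the article does not say how d was standardised, so they show plausibility and not an expected value.

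**Step 4: what the controlled comparison can deliver.** With 128 evaluable per arm, treated as independent, two-sided 5%:
- d = 0.35: power 80%.
- d = 0.25: power about 51%.
- d = 0.25 with baseline adjustment: the SD shrinks by √(1 − r²). At an assumed correlation r of 0.4 to 0.6, power is about 58% to 70%.
- 80% power at d = 0.25 unadjusted needs 252 evaluable per arm, so 252/0.60 = 420 recruited per arm and 840 in total.

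**Step 5: what it cannot deliver.** Suppose only depot patients enter 0.3 SD below their usual level and recover fully, with r = 0.6 and no drug effect (all assumed). At month 12 the arms are equal, but adjustment adds back r × 0.3 = 0.6 × 0.3 = 0.18 SD in favour of depot. In simulation this gave a false finding for depot in about 42% of studies with 128 per arm and 63% with 213 per arm.

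**The case against.** The strongest defence is that the plan is internally consistent as a before-after study. The Objectives section is neutral, and the endpoint, the null hypothesis, the paired test and the 128 patients all describe the same quantity. The baseline-adjusted comparison with controls is prespecified, listed first among the secondary outcomes in Table 1, and has a stated detectable effect. This stands: the controlled analysis is present. The defect is that the Abstract, Hypothesis and Discussion attach a causal reading to a test that cannot carry it.

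Three stronger readings are tempting, and the documents do not support them.

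- A reader might infer that depot patients enter because they are doing badly, so that regression to the mean is certain. The Treatment section says only: "Patients who were facing problems with their previous OST medication might benefit from study participation". The arm-specific inclusion criterion is willingness to be treated. Regression to the mean is possible, and its size cannot be taken from the document.
- A reader might infer that the matched controls would remove these biases if their comparison became primary. Controls are patients unwilling to switch. They are matched on gender, treatment duration, take-home status and functioning, but not on baseline OSTQOL. Step 5 shows that a dip confined to the depot arm would survive the adjustment.
- A reader might infer that the primary endpoint must be replaced at no cost. At d = 0.25 the comparison has about 51% power unadjusted, and recruitment began in April 2020 with ethics approval in place. Replacement is a trade-off and is not required to resolve the problem.

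**Conclusion.** The point holds as a mismatch between the primary test and the claim attached to it. A significant primary result shows that quality of life rose during depot treatment. It does not show that depot buprenorphine caused the rise or did better than usual treatment.

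Under a shared non-specific change of 0.10 to 0.40 SD of change, the test succeeds in 20% to 99% of studies with 128 completers and no depot advantage. That range is an assumption. The cited before-after gains with non-depot products make it credible without fixing a value. The conclusion does not depend on regression to the mean, because newly admitted patients and time trend are enough to raise it.

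The controlled comparison is the better basis for an effect claim. It reduces confounding and regression to the mean but does not eliminate them.

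**What to change.** 1. Align the objective in the Abstract and Discussion, and the Hypothesis, with the neutral wording of the Objectives section.
2. State that the within-arm result will be interpreted only as change under depot treatment.
3. Add the missing comparator of the primary test to the limitations.
4. State that an effect of depot buprenorphine will be claimed only if the planned baseline-adjusted depot-minus-control OSTQOL difference at month 12 is also significant. It can be a key secondary endpoint or a jointly required co-primary. Since both results must be significant, alpha need not be split.
5. State with that comparison that it is non-randomised, that controls are unwilling to switch, and that baseline OSTQOL is not a matching variable.

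Items 1 to 3 and 5 are wording. Item 4 needs no new patients or assessments if d = 0.35 is accepted as the target for the deciding comparison. The price is power: about 51% at d = 0.25 unadjusted. Making it co-primary would also mean a documented amendment during the study, and the key-secondary route is lighter.
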